### Recruitment and criteria for inclusion and exclusion

Physicians and therapists in the Danish municipalities of Copenhagen and Frederiksberg (henceforth collectively referred to as Copenhagen) are informed of the CapOpus trial through meetings and leaflets. In particular, OPUS, CMHC, and ACT-teams are targeted. Patients referring themselves and patients referred by general practitioners will be associated with one of these institutions prior to inclusion.

Inclusion criteria are presented in Table 1. The diagnostic criteria are based on the ICD-10 system [39].

**Table 1 T1:** Criteria for inclusion and exclusion in the CapOpus trial.

Inclusion:	Exclusion:
ICD-10 diagnosis F2 (F20–F29): Schizophrenia, schizotypal and delusional disorders	ICD-10 diagnosis F10.2: Alcohol dependence syndrome
	ICD-10 diagnosis F11.2: Opioid dependence syndrome
ICD-10 diagnosis F12: Mental and behavioral disorders due to use of cannabinoids	ICD-10 diagnosis F14.2: Cocaine dependence syndrome
Aged 18–35 years	Refusal to give informed consent
Residence in the Copenhagen area	
Sufficient Danish-speaking capabilities	
Able and willing to give informed consent	

The age group is selected both to ensure a relatively homogenous group of patients, and to reflect the age group at highest risk of developing schizophrenia [40]. The criterion for residence in the Copenhagen area is an attempt to maximize adherence to treatment by minimizing the distance to treatment facilities. If this criterion leads to insufficient numbers of included patients, expansion of the geographic area of the trial will be considered.

Patients must speak and understand Danish sufficiently to participate in both treatment and assessment without an interpreter.

The diagnostic criteria for exclusion are chosen so as to decrease the risk of treatment effects becoming confounded by the presence of other dependence syndromes. Only dependence syndromes of alcohol, opioids, and cocaine are cause for exclusion – more sporadic uses of these substances are not.

### Assessments

Patients are subjected to three almost identical assessments. The first assessment occurs at baseline before randomization, because information from the baseline assessment is used to perform stratified randomization and to validate inclusion and exclusion criteria. The second assessment occurs six months after the baseline assessment, when the treatment programs have just finished. The final assessment occurs ten months after the baseline assessment, in order to evaluate longer-term effects of the treatments. The contents of the assessments are outlined in figure 3 and explained in the following sections. The standard assessments are conducted at all three assessment points.

**Figure 3 F3:**
[figure not shown]
Assessment tools used in the CapOpus trial.

#### *Severity of abuse

Assessment of number of days with cannabis use in the past 30 days will be measured at all three assessment points using the TLFB [29]. The TLFB has been reported to have high validity in measuring cannabis consumption when compared with urinalysis [30]. Briefly, the TLFB is a self-reported measurement tool in which the respondent plots all memorable dates within a preceding period on a calendar, and then uses these dates to aid in remembering consumption of a given substance on each day in the period. If the patients consent, self-reported cannabis consumption will be validated with blood samples.

Apart from using the TLFB, information will be obtained about age of first use of cannabis, age of first regular use of cannabis, and reasons for use of cannabis.

#### *Influence and severity of other substance use

The WHO's Schedules for Clinical Assessment in Neuropsychiatry (SCAN) interview's chapters 11 and 12, excluding the section on nicotine, will be used to estimate influence and severity of other substance use, as well as influence of cannabis abuse [41]. Chapter 11 measures influence and severity of alcohol use, and chapter 12 of other psychoactive substances, including prescription medicine.

#### *Psychosis symptoms and clinical improvement

Psychosis symptoms are assessed by the use of The Positive and Negative Syndrome Scale (PANSS) for schizophrenia [42]. Changes in PANSS scores have been shown to correlate well with clinical improvements as measured by the Clinical Global Impressions Ratings (CGI) scale [43-45]. Furthermore, the overall impression of symptoms and functioning is evaluated using the Global Assessment of Functioning (GAF) scale [46,47].

#### *Cognitive function

Various aspects of cognitive function will be measured using a range of psychometric instruments. Prepsychotic intelligence will be estimated using the Danish Adult Reading Test (DART), a Danish adaptation of the National Adult Reading Test [48]. Speed of information processing will be assessed using the Brief Assessment of Cognition in Schizophrenia (BACS) symbol coding and Trail Making Part A [49-51]. Attention and vigilance are assessed by Continuous Performance Test, Identical Pairs version (CPT-IP) [52]. Working memory is assessed using Trail Making Part B. Memory and verbal learning are assessed with Hopkins Verbal Learning Test [53]. Executive functioning is assessed with Neuropsychological Assessment Battery (NAB) Mazes [54].

#### *Social functioning and quality of life

Social functioning within the major life areas of community, social, and civil life will be estimated using the 12-item interviewer administered version of the World Health Organization's Disability Assessment Schedules (WHODAS-II) [55]. Two measures of quality of life (QOL) will be used in a combined attempt to compare QOL improvements in the two treatment arms, namely the five-item EQ-5D [56] and the seventeen-item Manchester Short Assessment of Quality of Life (MANSA) [57].

#### *Sociodemographic variables

A number of sociodemographic variables will be assessed, including age, sex, living conditions, marital status, education, employment status, number of children, ethnicity, and history of homelessness.

#### *Other assessment tools

All of the assessment tools mentioned above will form the standard assessments that will be used at all three assessment points and on all patients. In addition, a few other assessment tools will be used. At six months follow up, user satisfaction with the received treatment will be evaluated using the eight-item Client Satisfaction Questionnaire (CSQ) [58]. Adherence to the CapOpus intervention will be measured by number of contacts between CapOpus consultants on one side and the patient, the patient's family, and the patient's case manager on the other side. Finally, cost of treatment and cost-benefit estimation will be performed by comparing number of outpatient treatments and number of bed days in the two treatment arms. This will be done register-based in The Danish Psychiatric Central Register [59,60] and The Danish National Hospital Register [61], as all persons in Denmark are easily identifiable in registers using a unique personal identification number given to all people either at birth or upon migration into Denmark [62].

### Randomization and blinding

Randomization into one of the two treatment arms is performed after the baseline assessment. Firstly, randomization is stratified by severity of cannabis abuse as measured by TLFB, by creating two sub-strata; one of patients having used cannabis less than 15 days in the preceding 30 day period, and one of patients having used cannabis 15 days or more. This is done to avoid the risk of heavy-users of cannabis being overrepresented in either of the treatment groups. Similarly, randomization will be stratified based on the referrer – OPUS, CMHC, or ACT, as it is unlikely that patients from these three referrers are comparable with regard to psychotic symptoms and level of functioning.

The Copenhagen Trial Unit (CTU) will perform the centralized randomization, and only the CTU will know the block size used to randomize. A research assistant provides information on the patients to the CTU after conducting the baseline assessment. The CTU then performs the randomization procedure based on computer-generated allocation sequences, and communicates the allocated treatment to the CapOpus consultants responsible for the CapOpus experimental intervention. If a patient is allocated to CapOpus intervention, the consultants contact the patient. Regardless of allocation, the consultants also contact the patient's case manager, so that the treatment as usual intervention can be commenced. This procedure ensures that the research assistant, who will be doing the subsequent patient assessments, is blinded to the allocated intervention. Blinding is maintained until the end of the trial. Patients are instructed not to reveal details that may cause the research assistant to deduce which treatment they are receiving. At each of the follow-up assessments, the research assistant will register a guess as to which treatment the patient is receiving. When the trial is finished, inter-rater reliability between the actual treatment and the research assistant's guess will be estimated using Cohen's kappa coefficient [63] to assess the degree to which blinding has been successful.

### Sample size and power calculation

A 2008 Cochrane review of psychosocial interventions for people with both severe mental illness and substance misuse [28] identified five papers with results from studies using a combination of motivational interviewing and cognitive behavioral therapy.[22,64-67] However, only one of these contains information about reduction of days with cannabis abuse, but presents only the median, not the mean, and the range, not the standard deviation.[22] However, 6 months after start of treatment, this particular paper reported that those receiving integrated care had, as median, 20.62 percent of days abstinent from all substances, compared to 1.10 in the routine care group, i.e. a difference of 19.5. Extrapolating this to our study, with a TLFB-period of 30 days, corresponds to 5.85 days. Truncating this to a more conservative 5 days, and assuming a standard deviation also of 5 days, it becomes possible to calculate sample size for an independent samples t-test; with an α-level of 0.05 and a power of 0.90, the required number of patients in each intervention can be calculated to be 22. Due to attrition, more patients will be required. Results from the OPUS trial, which may be comparable to our study in terms of participant profiles, showed that high attrition may be expected among substance-using people with schizophrenia [38]. We obtained data about one-year dropout from the OPUS trial among people with substance misuse, and found that among those receiving the control treatment, the dropout-rate was 37%. Generalizing this to our study, regardless of intervention allocation, at least 35 patients will be required in each of the two intervention groups. However, we aim to include between 60 and 70 patients in each group, as this would enable us to stratify the analyses. With 60 or 70 patients, it should also be possible to measure even smaller differences in secondary outcomes.

### Statistics

The main null-hypothesis to be tested is that there is no difference between the two treatment arms with regard to decrease in cannabis use. All randomized patients will be analyzed, including those who stop receiving treatment, according to the intent-to-treat principle [68]. Continuous outcome measures, including the primary outcome of reduction of days with cannabis abuse, will be analyzed using multivariate analysis of variance (ANOVA) mixed models with repeated measurements. This will include interaction analyses of time and type of treatment, in order to evaluate the effect over time. Binary outcome measures will be analyzed using multivariate logistic regression models. The subgroup of patients who complete the entire experimental treatment will be compared with all those randomized into the trial in order to determine risk factors for attrition. Sensitivity analyses will be carried out to evaluate the effect of treatment in patients that are inaccessible for follow-up. This will be conducted by multiple imputation methodology both using last observation carried forward, and assuming an increase in cannabis use among those lost to follow-up.

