### Objectives of the CapOpus trial

We plan to undertake a trial in which combined group-based and individual treatment, incorporating motivational interviewing, psycho-education, cognitive behavioral therapy, and social skills training in addition to treatment as usual, is compared with treatment as usual. The primary outcome will be change in number of days abstinent from cannabis within the preceding 30-day period as measured with the Time-Line Follow Back (TLFB) instrument [29,30].

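### The primary mixed model targets change through a time-by-treatment interaction and names no baseline or stratum adjustment; stating one would gain precision at no cost

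*Protocol article*

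**What the plan says.** Under Objectives, the article defines the outcome as a change: "The primary outcome will be change in number of days abstinent from cannabis within the preceding 30-day period". The Statistics section tests the null hypothesis that "there is no difference between the two treatment arms with regard to decrease in cannabis use". Continuous outcomes "will be analyzed using multivariate analysis of variance (ANOVA) mixed models with repeated measurements", and the section adds: "This will include interaction analyses of time and type of treatment, in order to evaluate the effect over time". It names no covariate, and it does not say whether baseline is a response or a covariate, or whether baseline means may differ between arms. The word *multivariate* is not defined.

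The Severity of abuse section shows that the baseline value is available: "Assessment of number of days with cannabis use in the past 30 days will be measured at all three assessment points using the TLFB". Under Randomization and blinding, "randomization is stratified by severity of cannabis abuse as measured by TLFB", with a cut at 15 days of use in 30, and "randomization will be stratified based on the referrer" (OPUS, CMHC or ACT). The sample size section mentions stratified analyses once: "we aim to include between 60 and 70 patients in each group, as this would enable us to stratify the analyses". It does not say by which factor, or whether the primary analysis is meant.

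**The concern.** Outcome, hypothesis and model all point at change from baseline. A repeated-measures model with baseline as a response, separate baseline means by arm and a time-by-treatment interaction estimates the difference between arms in mean change. That contrast subtracts the whole of a chance baseline difference. Adjustment subtracts only the part that predicts follow-up, so the change-score contrast usually has the larger variance.

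The trial also built baseline use and referrer into the randomisation, and the Statistics section does not carry either into the model. If a stratification factor is prognostic and is left out, the balance it bought is not reflected in the standard error, which is then too large rather than too small.

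What is at stake is precision. The sponsor calls the trial rather small, expects 37% attrition, and hopes to detect smaller differences on secondary outcomes. The Statistics section applies the same model to all continuous outcomes, so PANSS and GAF are affected as well as cannabis days.

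**Working it through.** **Inputs from the protocol article.** Target difference 5 days, SD 5 days (not said whether of the follow-up value or of change), alpha 0.05, power 0.90, dropout 37%, aim of 60 to 70 per arm. **Assumptions, not in the documents.** Baseline to follow-up correlation rho, and the ratio k of baseline SD to follow-up SD.

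**1. The plan's own figures.** The normal approximation gives n = 2 × (1.96 + 1.282)² × (5/5)² = 21.01, so 22 per arm (an exact t calculation gives 23, with power 0.8997 at 22). Attrition: 22/0.63 = 34.9, so 35. Both stated figures reproduce, with a two-sided test. With 60 to 70 per arm, 60 × 0.63 = 37.8 and 70 × 0.63 = 44.1, or about 38 to 44 evaluable.

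**2. Variance per patient, equal SDs.**
- Change score: 2(1 − rho)SD²
- Baseline-adjusted: (1 − rho²)SD²
- Ratio: 2/(1 + rho)

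| rho | variance ratio | SE wider by | SE at 60 per arm, SD 5: change | adjusted |
|---|---|---|---|---|
| 0.3 | 1.54 | 24% | 1.08 | 0.87 |
| 0.5 | 1.33 | 15% | 0.91 | 0.79 |
| 0.7 | 1.18 | 8% | 0.71 | 0.65 |

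The generalised least squares variance of the 6-month contrast in a three-visit mixed model (60 per arm, compound symmetry) gives the same SEs: the change column with baseline means free by arm, the adjusted column with baseline means constrained equal.

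**3. Unequal SDs.** In units of the follow-up variance, the change score has variance 1 + k² − 2k·rho = (1 − rho²) + (k − rho)². The ratio is therefore 1 + (k − rho)²/(1 − rho²), which is never below 1 and equals 1 only when k = rho.

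| k | rho 0.3 | rho 0.5 | rho 0.7 |
|---|---|---|---|
| 1 | 1.54 | 1.33 | 1.18 |
| 0.75 | 1.22 | 1.08 | 1.01 |
| 0.5 | 1.04 | 1.00 | 1.08 |

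Above k = 1 the ratio rises.

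**4. Power for 5 days at 38 to 44 evaluable per arm (two-sample t).**
- SD 5 as the SD of change: 99.0 to 99.6% unadjusted, at least 99.6% adjusted for rho 0.3 to 0.7.
- SD 5 as the follow-up SD, k = 1, rho 0.3: 95 to 97.5% unadjusted, 99.5 to 99.8% adjusted. At rho 0.5 or above, both are at least 99%.
- Illustration with a larger follow-up SD of 7, k = 1, rho 0.3 (assumptions): 74 to 80% unadjusted, 90 to 94% adjusted.

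**5. Detectable difference.** With SD 5 as the SD of change, k = 1 and 37.8 evaluable per arm, the difference detectable at 90% power is 3.24 × 5 × √(2/37.8) = 3.73 days unadjusted. Adjusted, it is 3.01, 3.23 and 3.44 days at rho 0.3, 0.5 and 0.7.

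**The case against.** The strongest reply is that the article names a class of models and leaves the parametrisation open. It does not say that baseline means are free. A mixed model with time-by-treatment terms and equal baseline means fits the wording and recovers the full precision. This is a condensed article, an analysis plan may exist, and a covariate list commonly belongs there. The sample size section does mention stratifying the analyses. Baseline use, as a response, is not ignored even in the ordinary form of the model.

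Most of this stands. A reader might infer that the plan refuses to use baseline and strata; the text supports only that it does not name them. What remains is that outcome, hypothesis and interaction term are all stated in terms of change, and the usual fit of such a model leaves baseline means free. The remark on stratified analyses names no factor and is tied to the larger sample, so it cannot be read as a commitment to covariate adjustment.

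A second reply is that power is ample. At the protocol's SD of 5 it is, as step 4 shows. A reader might infer that the trial is underpowered without adjustment, but that follows only from a larger SD, which is a separate question about the sample size assumption.

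A third reply concerns the strata. The 15-day split adds little once continuous baseline days are in the model. The protocol justifies the referrer stratum by symptoms and functioning, not by cannabis use, so its gain for the primary outcome cannot be quantified. Both points are right.

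**Conclusion.** The point holds as an efficiency improvement. In its ordinary form, the stated model yields a change-score contrast that is at best as precise as a baseline-adjusted one. The excess variance is 54%, 33% and 18% at rho 0.3, 0.5 and 0.7 with equal SDs, and 22%, 8% and 1% if the baseline SD is three quarters of the follow-up SD. The direction is certain for the unconstrained model. The size rests on rho and the SD ratio, which the documents do not give.

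The documents do not support three stronger readings: that the analysis is biased, that it contradicts the design, or that the primary comparison lacks power on the protocol's own figures. Leaving out the strata makes standard errors conservative at most. The practical benefit is narrower intervals, a margin if the SD exceeds the assumed 5 days (which the protocol adopts because its source gave no SD), and better precision on secondary outcomes.

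**What to change.** State the primary model in full, before unblinding:

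- Responses: days of cannabis use in the past 30 at 6 and 10 months. Terms: treatment, visit, treatment-by-visit, continuous baseline days and baseline-by-visit.
- Equivalently, keep all three visits as responses and constrain baseline means to be equal between arms. This form also retains patients who have only a baseline value.
- Include referrer (OPUS, CMHC, ACT) as a covariate. The 15-day severity stratum is optional once continuous baseline is in.
- Use the same form, with its own baseline, for PANSS, GAF and the other continuous outcomes.

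The cost is wording only. Baseline days and referrer are already known before randomisation, so no extra data or patients are needed. Fixing the form in advance also removes any later choice between a change-score and an adjusted result.

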## Methods

The trial is designed as a two-armed, parallel-group, observer-blinded randomized clinical superiority trial (Figure 1). Patients will receive either specialized CapOpus treatment or treatment as usual, as described below.

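### Risk factors for attrition are sought by comparing completers of the experimental treatment with everyone randomised, a group that contains those completers and the whole control arm

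*Protocol article*

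**What the plan says.** The Statistics section of the protocol article describes one attrition comparison. It names both groups, "The subgroup of patients who complete the entire experimental treatment will be compared with all those randomized into the trial", and the purpose, "in order to determine risk factors for attrition". It names no test or model for this comparison.

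Three other places show who can complete the experimental treatment:

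- Methods, opening paragraph: "Patients will receive either specialized CapOpus treatment or treatment as usual".
- Randomization and blinding: "If a patient is allocated to CapOpus intervention, the consultants contact the patient". For controls, the consultants contact only the case manager.
- Other assessment tools: "Adherence to the CapOpus intervention will be measured by number of contacts between CapOpus consultants on one side". The stated adherence measure exists only for the CapOpus intervention.

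Nothing elsewhere in the article narrows the comparator to non-completers or to the experimental arm.

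**The concern.** A risk factor for attrition is a characteristic that differs between patients who stay and patients who leave. The stated comparison does not separate these two groups. Its comparator is a mixture of three:

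- the completers, who therefore stand on both sides;
- the controls, who are neither completers nor dropouts of the experimental treatment;
- the experimental-arm non-completers, who are the only patients the question is about.

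The first two groups pull the comparator towards the completers' own profile. A real predictor of non-completion then looks weaker than it is, and a null result could be read as evidence that completers and non-completers are alike. The sample size section applies a 37% dropout rate to both arms, so who leaves is a practical question in this trial.

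**Working it through.** **The plan's own figures.** The article gives no figure for the attrition comparison. Its sample size inputs do reproduce. A difference of 5 days, SD 5, α = 0.05 two-sided and power 0.90 give 22.02 per arm by the t-test solution (article: 22). With 37% dropout, 22 / 0.63 = 34.9, rounded up to 35 (article: 35).

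**Inputs for the check**

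- From the article: a target of 60 to 70 per arm (midpoint 65 used here) and 37% dropout.
- Assumption: 37% serves as the non-completion share d in the experimental arm. In the article it is one-year dropout under the control treatment of another trial, so d = 0.20 and d = 0.50 are shown too.
- Assumption: a baseline factor is present in p_c = 30% of completers and p_n = 60% of non-completers.

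**Step 1: who is in the comparator.** At 65 per arm and d = 0.37, completers number 65 × 0.63 ≈ 41 and non-completers 65 × 0.37 ≈ 24. The comparator of 130 is then:

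- 41 completers (31.5%), also in the other group;
- 65 controls (50%);
- 24 experimental-arm non-completers (18.5%).

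These shares do not depend on arm size. As d goes from 0.20 to 0.50, the overlap falls from 40% to 25% and the non-completers rise from 10% to 25%. Controls are always 50%.

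**Step 2: expected contrast, all randomised minus completers.** Randomisation gives both arms the same expected prevalence of a baseline factor, so

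prevalence in all randomised = (1 − d)·p_c + d·p_n

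contrast = (1 − d)·p_c + d·p_n − p_c = d·(p_n − p_c)

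The retained fraction is d, whatever the prevalences. In the illustration (true difference 30 points, odds ratio 3.5):

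| d | All randomised | Contrast (points) | Fraction kept | Odds ratio |
|---|---|---|---|---|
| 0.20 | 36.0% | 6.0 | 20% | 1.31 |
| 0.37 | 41.1% | 11.1 | 37% | 1.63 |
| 0.50 | 45.0% | 15.0 | 50% | 1.91 |

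**Step 3: the milder reading, completers against everyone else randomised (41 vs 89).** This removes the overlap but keeps the controls. Prevalence in the rest is (24 × 0.60 + 65 × 0.411) / 89 = 41.1 / 89 = 46.2%, so the contrast is 46.2 − 30 = 16.2 points instead of 30.

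**Step 4: power in the illustration.** Simulation with 40,000 runs, pooled two-proportion tests, 41 completers, 24 non-completers and 65 controls:

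| Comparison | Power | Type I error |
|---|---|---|
| Completers vs all randomised, tested as if independent | about 17% | about 0.6% |
| Completers vs all others randomised | about 42% | about 5.0% |
| Completers vs non-completers, experimental arm only | about 68% | about 5.1% |

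The low type I error in the first row comes from the overlap. With a common variance, the independent-samples standard error exceeds the correct one by √[(1/41 + 1/130) / (1/41 − 1/130)] = √(0.03208 / 0.01670) = 1.39.

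**The case against.** The best defence is that the sentence is loose. No test is named. It could mean a descriptive table of how completers differ from the randomised population, or a logistic regression of completion among all randomised, since the section assigns logistic regression to binary outcomes. On the regression reading there is no overlap, and the loss is the smaller one in Step 3. This part of the defence stands: the independence problem, the 1.39 factor and the 17% apply only if a two-sample test is run on the overlapping groups. The controls remain in the comparator on either reading, and a description of representativeness is not the purpose the sentence gives.

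A reader might also infer more than the article supports:

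- *Attrition in the control arm is ignored.* This is a condensed article, and the full protocol or analysis plan may hold a further analysis. Only the stated comparison can be faulted.
- *Stopping treatment is confused with loss to follow-up.* The Statistics section separates patients who stop treatment, kept under intention to treat, from those who cannot be reached for follow-up, covered by sensitivity analyses. At most, the word attrition is ambiguous in this one sentence.
- *The missing-data analyses are undermined.* They are described as last observation carried forward and an assumed increase in use. Neither is said to draw on predictors of attrition.
- *Real predictors will be missed.* The power figures belong to one assumed scenario. A strong predictor could still show.
- *A followed-up versus lost comparison across both arms would recover far more power.* That concerns a different event, so its power is not comparable with the figures above.

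**Conclusion.** The comparison is wrong as written for its stated purpose. That conclusion rests on the text alone: the article fixes both groups and the aim, and no control can complete the experimental treatment. The shrinkage to a fraction d follows from baseline balance and needs no assumed prevalence. The 30-to-11-point example and the power figures do depend on the assumed 65 per arm, 37% non-completion and 30%/60% prevalences. The importance is modest. This is a secondary, exploratory analysis, and neither the primary intention-to-treat test, the treatment-effect estimate nor the sample size depends on it.

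**What to change.** Change the one sentence so that patients who complete the experimental treatment are compared with those allocated to it who do not, within the experimental arm only, for example by logistic regression of completion on baseline factors. If attrition is also meant as loss to follow-up, state that as a separate comparison of assessed with not-assessed patients across both arms, with arm as a factor. If a description of how representative the completers are is also wanted, label it as that. The cost is a change of wording; the data already planned are enough.

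### A sensitivity analysis called multiple imputation uses last observation carried forward, a single fixed fill-in, so it understates the uncertainty about patients lost to follow-up

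*Protocol article*

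**What the plan says.** The Statistics section of the protocol article analyses the primary outcome in all randomized patients with "multivariate analysis of variance (ANOVA) mixed models with repeated measurements". It then adds a check on loss: "Sensitivity analyses will be carried out to evaluate the effect of treatment in patients that are inaccessible for follow-up". The method follows: "This will be conducted by multiple imputation methodology both using last observation carried forward". The second scenario named in that sentence is "assuming an increase in cannabis use among those lost to follow-up".

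Two other sections bear on this. Under Assessments, "Patients are subjected to three almost identical assessments": baseline, month 6 and month 10. The first measurement after baseline therefore comes only at the end of treatment: "The second assessment occurs six months after the baseline assessment, when the treatment programs have just finished". Under Sample size and power calculation, attrition is taken from the control arm of an earlier trial, in which "the dropout-rate was 37" percent at one year. That rate is applied to both arms here.

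**The concern.** Multiple imputation draws several plausible values for each missing one, and the spread between the completed data sets carries the uncertainty about what was not seen. LOCF makes no draws. A sensitivity analysis cannot be both.

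The visit schedule makes this sharper. A patient lost before month 6 has only the baseline value to carry forward, so LOCF sets that patient's change to zero by construction. The analysis is meant to examine the effect in patients who could not be followed, but it fixes their change in advance and treats it as data.

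At stake is the robustness statement in a trial that expects heavy attrition. This is one of two named checks on loss. If it is reported as multiple imputation, readers will believe that uncertainty about lost patients has been carried when it has not.

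**Working it through.** **The plan's own figures.** Inputs from Sample size and power calculation: effect 5 days, SD 5 days, alpha 0.05, power 0.90, dropout 37%.
- n per arm = 2 × (1.960 + 1.282)² × 5²/5² = 21.01, rounded up to 22.
- With dropout: 22 / 0.63 = 34.9, rounded up to 35.

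Both stated figures reproduce (two-sided test, normal approximation).

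**The label.** Under Rubin's rules, total variance = W + (1 + 1/m)B, where W is the within-imputation variance, B the between-imputation variance and m the number of imputations. LOCF puts the same value in every data set, so B = 0 and the total is W, whatever m is. That is single imputation.

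**The size.** Assumptions beyond the documents: SD 5 applies to the change score; all loss d occurs before month 6, completely at random and equally in both arms; a change-score comparison stands in for the mixed model. With n per arm and mean change μ in an arm:
- LOCF difference = (1 − d) × 5.
- LOCF variance of change per arm = (1 − d) × 25 + d(1 − d) × μ².
- Observed-data SE = √(2 × 25 / (n(1 − d))).

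For n = 60, d = 0.37, control μ = 0 and CapOpus μ = 5:
- Difference = 0.63 × 5 = 3.15 days.
- Variances: control 15.75; CapOpus 15.75 + 5.83 = 21.58. LOCF SE = √(37.33/60) = 0.79.
- Observed-data SE = √(50/37.8) = 1.15. The ratio is 0.69, so the LOCF interval is 31% narrower.
- With nobody lost, the SE would be √(50/60) = 0.91. LOCF with 37% missing looks more precise than complete data.
- The nominal 95% LOCF interval covers 5 days about 35% of the time.

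The same calculation at other loss rates (60 per arm):

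| Loss | LOCF difference | LOCF SE (control change 0) | Observed-data SE | SE ratio, control change 0 to 5 days |
|---|---|---|---|---|
| 37% | 3.15 | 0.79 | 1.15 | 0.69 to 0.87 |
| 20% | 4.00 | 0.86 | 1.02 | 0.84 to 0.98 |
| 10% | 4.50 | 0.89 | 0.96 | 0.92 to 1.01 |

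**What depends on the lost patients.** Simulation, 65 per arm, 37% loss in both arms, 20,000 runs:
- Lost patients change like completers: truth 5.00, LOCF 3.15, coverage 32% (41% if controls improve by 2.5 days).
- Lost patients' mean change is zero: truth 3.15, LOCF 3.14, coverage 95%.
- Lost patients worsen by 5 days in both arms: truth 3.15, LOCF 3.14, coverage 95%.
- No true effect: rejection rate 5.0% to 5.2%.

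**Unequal loss, no true effect.** Take 37% loss in control and 20% in CapOpus (the 20% is an assumption, not in the documents), with both arms improving by 5 days. The spurious difference is (0.37 − 0.20) × 5 = 0.85 days, with about 16% false positives at 60 per arm. With 2.5 days' improvement the difference is 0.43 days.

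**The case against.** A reader might infer that LOCF makes the estimate biased and its interval far too narrow. The documents do not support that as a flat statement.

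- **Bias is conditional.** The 3.15 against 5 needs lost patients to resemble completers. If their mean change is zero, or they change equally in both arms with equal loss, the LOCF difference is unbiased. The false-positive case needs unequal loss, whereas the plan assumes one rate for both arms.
- **The SE is not wrong for the estimator.** In the first simulation above, the mean LOCF SE was 0.756 and the empirical SD 0.755. The poor coverage there comes mainly from bias. What is lost is uncertainty about the zero-change assumption itself.
- **The 37% is generous for month 6.** It is a one-year, control-arm rate from another trial. Patients lost between months 6 and 10 carry a real month-6 value.
- **A scenario may impose an assumption.** Return-to-baseline imputation with random draws gives about 3.1 days under the same inputs, so the shrinkage comes from assuming zero change, not from the mislabel.
- **The primary analysis does not use LOCF,** and the second scenario is deliberately pessimistic.
- **A condensed article** normally leaves imputation models and pooling to the full protocol or analysis plan.

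The first five points stand, and they limit the size and reach of the concern. The last does not remove it: the article does not merely omit detail, it names a method that contradicts its label. A zero-change scenario is legitimate, but calling it multiple imputation is not, because none of the uncertainty is carried.

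**Conclusion.** The point holds in a limited form and should be corrected. LOCF is a single fixed fill-in described as multiple imputation. It enters zero change as observed for everyone lost before month 6 and understates the uncertainty about those patients.

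With the plan's effect and SD, 60 per arm, 37% lost before month 6 completely at random and no control change, the result is 1.85 days too low, with an SE 31% below that of an observed-data analysis. At 20% loss the shortfall is 1 day and the SE is 2% to 16% lower; at 10% loss it is 0.5 days, with an SE between 8% lower and about equal. The shortfall counts as bias only if lost patients would have changed like completers. Unequal loss with common improvement can create a difference from nothing; equal loss with no true effect does not inflate false positives.

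It would be wrong to infer that the primary test is compromised: the repeated-measures mixed model and the sample size are untouched. What suffers is the robustness statement.

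**What to change.** Replace the sentence. Impute month-6 and month-10 days by arm from baseline days, the stratification factors, any observed follow-up value and the register data on bed days and outpatient contacts. Use random draws kept within 0 to 30 days, for example by predictive mean matching, and combine with Rubin's rules.

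This imputation rests on much the same missing-at-random assumption as the mixed model, so it does not replace a pessimistic check. Run that check within the same framework, either as a stated shift toward more use among those lost, by arm, or as reference-based or return-to-baseline draws. Return-to-baseline draws correct the uncertainty but keep the zero-change shrinkage, and the report should say so.

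If a zero-change LOCF scenario is kept, label it single imputation and do not report it as multiple imputation.

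The cost is one sentence of wording, a little programming and a wider sensitivity interval. No new data are needed.
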